### Thoracoabdominal Kinematics

Thoracoabdominal kinematics will be evaluated by optoelectronic plethysmography (BTS), as previously described [36]. Briefly, a video is recorded with 8 solid-state charge-coupled cameras operating at 100 frames per second and synchronized with an infrared flashing light-emitting diode. Four cameras will be positioned in front of the participant and 4 behind; 89 retroreflective markers will be placed on the anterior and posterior sides of the trunk according to a previously described protocol [37]. A 3D calibration of the equipment will be performed on the basis of the manufacturer’s recommendations. The assessment will be performed with the individual on a cycle ergometer at 3 time points, that is, at rest, during the unloaded exercise, and at 75% W_peak_, according to the values obtained from CPET. The data analysis will use an average of 6 homogeneous respiratory cycles.

### Allocation, Randomization, and Blinding

Eligible patients will be randomly allocated to either BD or placebo interventions. The randomization sequence will be computer-generated and placed in sealed, opaque, and numbered envelopes by a volunteer not involved in the study. The researcher who will provide the intervention (BD or placebo) will open the envelopes and will not be involved in the data collection or analysis. The participants will not be informed if they will receive BD or placebo intervention. The BD and placebo inhaler devices will be identical to the pressurized metered dose type. All the assessments will be performed by a blinded assessor for the interventions.

### Interventions

Participants will be instructed not to consume alcohol or coffee or perform intense physical activity the day before the exercise test. In addition, they will be oriented to suspend routine BD medication for 6 hours for short-acting β-2 agonists and for 12 hours for short-acting muscarinic antagonists, and for 24 hours for long-acting β-2 agonists and 48 hours for long-acting muscarinic antagonists before the exercise test, according to the European Respiratory Society 2019 guidelines [22]. In case of exacerbation of symptoms during the period of BD suspension, the patient will be advised to use the medication, and the test will be rescheduled.

According to the randomization, a trained respiratory physiotherapist will administer either BD or placebo, ensuring proper treatment timing by using a timer and correct inhaler technique. Missed sessions will be rescheduled according to the participant’s availability to improve patient adherence. The intervention will combine 2 BD compounds: ipratropium (20 µg) and fenoterol (50 µg). Ipratropium is a short-acting antimuscarinic agonist, and fenoterol is a short-acting β-2 agonist BD. The BD or placebo will be delivered to the patient via a pressurized metered-dose inhaler with a spacer at least 20 minutes prior to CWRET, and CWRET will be performed no more than 1 hour after the administration of BD or placebo.

### BD and Placebo Delivery

The participants will be asked for total exhalation, followed by appropriate placement of the spacer mouthpiece with a nasal clip, and the first 8 puffs (30-second intervals between puffs, controlled by a timer) will be delivered through the opposite end of the spacer. The participants will be instructed to perform 5 tidal volume breaths for each puff. The total dose will consist of 160 µg of ipratropium and 400 µg of fenoterol.

### Outcomes

#### Primary Outcome

The primary outcome will be T_lim_ in CWRET. T_lim_ has been proposed as the main variable for assessing responsiveness to BDs in patients with chronic respiratory diseases [33]. A minimum clinically important difference >60 seconds has been suggested from improvements in clinical outcomes in BD trials [33,35]. T_lim_ will be determined by the inability to maintain a pedaling frequency below 60 rpm for more than 10 seconds despite verbal encouragement.

#### Secondary Outcomes

The following variables will be obtained from optoelectronic plethysmography: total chest wall and compartmental (upper ribcage, lower ribcage, and abdominal) volumes and TAA values. Thoracoabdominal kinematics will be compared during BD and the placebo effect. The associations between thoracoabdominal kinematics and CWRET variables will be determined.

#### Additional Measures

To appropriately describe the individuals with NCFB at baseline, basic demographic data and medical information, including age, smoking status, ethnicity, sex, anthropometric (height and weight) measures, and BD use, will be recorded. All reported clinical data will be confirmed in the hospital medical record review.

### Data Analysis

A sample of 39 participants was estimated as the number needed to provide 80% power to detect a between-group difference of 55.2 (SD 119.4) seconds in T_lim_, according to a pilot study (n=10; 80% females; 47.90 [SD 10.95]; FEV1 57.25% [SD 35.08%] predicted; FVC 69.12% [SD 31.21%] predicted; residual volume/total lung capacity 196% [SD 18.01%] predicted). The final sample size will be set at 45 patients, assuming up to a 10% loss during follow-up. The results will be analyzed according to the intention-to-treat principle to preserve the effects of group allocation and to provide an assessment of the practical impact of the intervention [38], as recommended by the CONSORT (Consolidated Standards of Reporting Trials) statement [39] (Multimedia Appendix 1). A median substitution will be imputed with the missing data. Data distribution will be assessed via the Kolmogorov‒Smirnov test. Comparisons between BDs and placebo data will be analyzed via 1-sided *t* tests or Wilcoxon tests for T_lim_ and repeated-measures analysis of variance or Friedman tests for thoracoabdominal kinematics variables. The number of participants who achieved the minimum clinically important difference (>60 seconds) in CWRET between BDs and placebo will be compared via chi-square tests. Pearson or Spearman correlation will be used to verify the associations between CWRET and thoracoabdominal kinematics variables. *P* values <.05 indicate statistical significance. The carryover, period, and sequence effects for T_lim_ will be estimated using generalized estimating equations models. If the carryover effect is not significant, a reduced model excluding the carryover term will be refitted. The statistical analysis will be performed using SPSS software (version 17.0; IBM Corp).

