## Results

This study was funded by São Paulo Research Foundation (FAPESP, grants 2018/17788-3) and Conselho Nacional de Desenvolvimento Científico e Tecnológico (grant 312.279/2018-3) for the CardioO2 system (Medical Graphics Corporation) and the optoelectronic plethysmography system, respectively. The ethics approval (3.008.886) was granted in November 2018. The pilot study commenced in April 2019 but was interrupted due to the COVID-19 pandemic in early 2020; it was restarted and completed in April 2022. As of December 2023, enrolling by invitation is the last status of Clinical Trials.gov PRS (NCT05183841). Consent was obtained from 39 patients until May 2025. Of the 39 consented patients, one was excluded due to difficulty performing the cycle ergometer test and 6 patients did not complete the protocol. Data collection is expected to continue until November 2025. Data analysis is anticipated to begin in 2025, with initial results anticipated to be reported on and published after the completion of data collection. The publication of results is anticipated to be in 2025-2026.

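### Filling missing values with a median and then testing them as observed understates the standard error of the primary Tlim comparison and generally raises its false-positive rate, modestly in the likelier case

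*Protocol article*

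**What the plan says.** All of the rules below stand in the Data Analysis section of the protocol article.

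- **Analysis set:** "The results will be analyzed according to the intention-to-treat principle to preserve the effects of group allocation".
- **Missing data:** "A median substitution will be imputed with the missing data". The sentence is not restricted to any one variable.
- **Primary comparison:** "Comparisons between BDs and placebo data will be analyzed via 1-sided" t tests or Wilcoxon tests for Tlim, where P "values <.05 indicate statistical significance".
- **Other models:** generalized estimating equations are planned to estimate carryover, period and sequence effects. Nothing says that they replace the test on filled data, or that they use unfilled data.

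The Results section reports on the 39 patients who had consented by May 2025: "one was excluded due to difficulty performing the cycle ergometer test and 6 patients did not complete the protocol". It does not say at which visit the six stopped.

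**The concern.** A single fixed fill adds rows to the data set without adding information. The t and Wilcoxon tests cannot tell a filled value from a measured one, so they count too many patients and see too little spread. The harm takes two forms.

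- **Both days filled.** Every such patient gets the same artificial difference between bronchodilator and placebo. The SD of the differences shrinks while n stays at its full value.
- **One day filled.** The patient's own value on one day is set against a group median on the other. That is no longer a within-patient contrast, and the Strengths and Limitations section rests the gain in power on the crossover design.

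At stake are the P value and the precision of the primary endpoint. The same fill can also decide whether a patient counts as exceeding the 60-second threshold, on the basis of a value that was never measured.

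**Working it through.** **Inputs from the protocol article.** Final sample 45, loss up to 10%, difference 55.2 s with SD 119.4 s, 1-sided test at 5% (all Data Analysis); allocation on day 2, immediately before the first constant work-rate test (Experimental Design); 39 consented, 1 excluded, 6 non-completers (Results).

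**Reproducing the plan's own figure.** The plan gives 39 patients for 80% power. A paired t test with standardised difference 55.2/119.4 = 0.462 and two-sided 5% gives n = 39 (power 0.803). So 119.4 s must be the SD of the paired differences, and I use it that way. A one-sided test would need only 31; that mismatch is a separate matter and does not affect this point. Allowing for loss, 39/0.90 = 43.3, so 44, against the 45 stated.

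**Closed form, whole difference filled with a constant.** If k of n differences are observed with SD s and the rest are set to a constant near their centre:

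- estimated SE = s × sqrt[(k−1)/(n(n−1))]
- true SE ≈ s/sqrt(k)
- ratio = sqrt[k(k−1)/(n(n−1))]
- actual one-sided error ≈ 1 − Φ(1.645 × ratio)

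With n = 45:

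| Filled | k | Ratio | One-sided error |
|---|---|---|---|
| 4 | 41 | sqrt(1640/1980) = 0.910 | 6.7% |
| 6 | 39 | sqrt(1482/1980) = 0.865 | 7.7% |
| 8 | 37 | sqrt(1332/1980) = 0.820 | 8.9% |

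With 8 filled, the true SE is 119.4/sqrt(37) = 19.6 s and the reported SE is 0.820 × 19.6 = 16.1 s.

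**Simulation of the t test under no effect.** Normal Tlim; n = 45; SD of differences 119.4 s; assumed within-patient correlation 0.3 to 0.85; each gap filled with the median of its condition; gaps unrelated to outcome and, for one-day gaps, balanced over conditions.

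| Pattern | 4 to 6 patients filled | 8 patients filled |
|---|---|---|
| One day filled | about 5.7-6.4% | about 7% |
| Both days filled | about 7-8% | about 9-10% |
| Complete pairs, no fill | about 5% | about 5% |

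The estimated SE was below the true SE in every setting.

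**Wilcoxon test** (assumed correlation 0.5 to 0.9, normal and log-normal Tlim). One day filled: 5.2-5.8% with 4 patients and 5.7-6.1% with 6. Both days filled: 7.2-8.0% and 9.3-9.9%.

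**Skewed Tlim with all gaps in one condition** (log-normal, 4 to 7 filled, t test). The median lies below the mean, so the estimate itself shifts. If all gaps are under bronchodilator, one-sided error falls to 3.6-4.5%. If all are under placebo, it rises to 6.7-9.9%. The SE is understated in both cases.

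**Precision.** At correlation 0.85 with one day filled, the average estimated SE is 20.4 s (6 filled) to 21.1 s (8 filled). Complete pairs give 119.4/sqrt(39) = 19.1 s and 119.4/sqrt(37) = 19.6 s. The filled analysis is thus less precise than dropping those patients, and its reported SE still understates its true one.

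**How often the rule may be used.** Non-completion so far is 6/38 = 15.8%, against the planned 10%. Applied to 45 patients, 15.8% is about 7 and 10% is about 4 to 5.

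**The case against.** The best defence concerns size, and most of it stands.

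- **Both days missing is not the natural case.** Allocation takes place on day 2 and the exercise test follows. A patient lost earlier was never randomised and has no obvious place in an intention-to-treat set. A randomised patient will usually have a day 2 value and lack only day 3. A reader might infer that the error roughly doubles to 9-10%. That needs 8 patients filled on both days, which the design makes unlikely.
- **The rate of missing Tlim is not known.** A reader might add the one exclusion to the six non-completers and quote 7 of 39, or 18%. The 39 are consents, and the excluded patient could not manage the cycle test and may never have been randomised. The timing of the six is not stated. The documents show that the rule is likely to be applied, but not how often.
- **The interval is not always narrower with the fill.** At high within-patient correlation, removing the fill narrows it.
- **The error does not always rise.** Skewed data with all gaps under bronchodilator push the one-sided error below 5%.

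One might add that a full analysis plan could exist. That does not answer the point: the article fixes the rule and the tests that follow it, and the objection is to that rule. The planned estimating-equation models do not answer it either, since they are assigned to carryover, period and sequence effects.

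**Conclusion.** The point holds. The plan commits to a single fill followed by tests that treat filled values as data. The reported SE is too small in every setting examined, and the false-positive rate generally exceeds 5%. In the likelier pattern, one day filled, the excess is about 1 percentage point with 4 to 6 patients and about 2 with 8. If both days were filled it would be about 2 to 3 points with 4 to 6 and 4 to 5 with 8.

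These sizes rest on assumptions that the article does not settle: within-patient correlation, the shape of the Tlim distribution, a fill by condition median, and gaps unrelated to outcome. The direction of the SE error does not depend on the particular correlation or distribution tried. The direction of the type I error does, when Tlim is skewed and the gaps fall in one condition. The documents do not support a claim of near-doubled error, of a known 18% missing, or of a uniform bias towards the bronchodilator. The rule still deserves correction before analysis, because it affects the primary test, gives a wrong SE and gains nothing.

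**What to change.** Delete the median substitution and run the primary Tlim comparison on observed values only, by one of two routes:

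1. complete pairs with the planned test; or
2. a linear mixed model with treatment, period and sequence as fixed effects and patient as random effect, so that a patient with one day contributes that day.

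Name one as primary now and report the other as a sensitivity analysis. Complete pairs alone restore the nominal error when gaps are unrelated to outcome, so the mixed model is an option and not a condition of the repair. Drop the fill from the 60-second responder count and the kinematics analyses as well.

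**Cost.** Removing the fill is a change of wording; choosing the mixed model would also replace the named primary test. Patients with no Tlim contribute nothing. The interval may widen or narrow, depending on the within-patient correlation. With 45 enrolled, 10% loss leaves 45 × 0.90 = 40.5 pairs, above the 39 required. Loss at 15.8% leaves 45 × 32/38 = 37.9, about 38, so little planned power is at risk. Data collection is expected to run to November 2025; the change should be made and dated before the data are analysed.

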**Methods:**

This crossover randomized controlled trial will involve 45 outpatients with NCFB aged 18 to 59 years. They will be evaluated in 3 visits. On day 1, the maximal exercise capacity (cardiopulmonary exercise test; peak work rate [W_peak_]) will be assessed. On day 2, individuals will be randomized to receive either BD (ipratropium bromide 160 µg and fenoterol hydrobromide 400 µg) or a placebo and then undergo simultaneous endurance exercise capacity (constant work-rate exercise test) and thoracoabdominal kinematics (optoelectronic plethysmography) assessments. After at least 1-week washout (day 3), the individuals will repeat the same assessments as on day 2 in the reverse order. The time to the limit of tolerance will be obtained in both groups (BD and placebo groups) as the primary outcome. Thoracoabdominal kinematics will be assessed at 3 time points: at rest, during unloaded exercise, and at 75% W_peak_. The total chest wall and compartmental volumes as well as thoracoabdominal asynchrony will be assessed. The assessors and patients will be blinded to the interventions (BDs or placebo). Data will be compared using 1-sided *t* tests or Wilcoxon tests and repeated-measures analysis of variance or Friedman tests. Categorical data will be analyzed using the chi-square test or Fisher test. The associations among variables will be analyzed using Pearson or Spearman correlation. The significance level will be set at 5% (*P*<.05).

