Despite the lack of robust studies demonstrating the effectiveness of BD use in the treatment of NCFB, BDs continue to be among the most commonly prescribed medications worldwide for this population [9,10]. A small previous study in adults with clinically stable NCFB revealed that combining inhaled corticosteroids with long-acting β-2 agonists might improve dyspnea and increase the number of cough-free days compared with high-dose inhaled corticosteroids, with no effect on the quality of life, number of hospitalizations, or lung function [11]. Despite being a randomized trial, neither patients nor assessors were blinded, and there was an overall high risk of bias, according to Goyal and Chang [12]. A more recent and larger study [13] evaluated the effects of 6-month tiotropium (long-acting muscarinic antagonists) treatment in 90 clinically stable adults with NCFB. Compared with placebo, tiotropium improved the forced expiratory volume in the first second (FEV1) by 58 mL and the forced vital capacity (FVC) by 78 mL. Nevertheless, there was no difference in the quality of life, chronic cough, exercise capacity, or neutrophil and eosinophil counts in the blood or sputum. Furthermore, it did not reduce the number of exacerbations. To date, there are no studies on the effect of BDs on the exercise capacity of this population.

In individuals with NCFB, airflow limitation and dyspnea are strongly associated with exercise capacity [14]. It seems plausible that BDs may improve the exercise capacity of individuals with NCFB similar to what has been observed in individuals with COPD. Additionally, thoracoabdominal asynchrony (TAA) is very prevalent in individuals with COPD and is associated with exercise limitations [15,16]. In this population, the main effect of BDs is an increase in the basal inspiratory capacity and changes in dynamic hyperinflation during exercise, which improves exercise capacity [17]. However, no study has evaluated TAA or the thoracoabdominal kinematics of individuals with NCFB. Therefore, we hypothesize that dual bronchodilation can improve the exercise capacity of individuals with NCFB and reduce TAA during exercise.

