## Methods

### Study Design

This is a randomized, placebo-controlled, double-blind, crossover trial (Figure 1). Participants are assigned in a 1:1 ratio to 2 treatment periods, each lasting 1 hour, with a 1-week washout period between them.

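### The sample size of 39 matches a two-sided 5% paired test, but the primary T_lim test is planned one-sided at P<.05, so the stated N and power do not belong to it

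*Protocol article*

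**What the plan says.** The trial is a two-period crossover in which each patient is tested under both conditions (Study Design: "This is a randomized, placebo-controlled, double-blind, crossover trial"). The primary outcome is T_lim in the constant work-rate test.

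- **Sample size (Data Analysis).** "A sample of 39 participants was estimated as the number needed to provide 80% power", and the sentence goes on "to detect a between-group difference of 55.2 (SD 119.4) seconds in T_lim". It cites a pilot of 10 patients. It gives no alpha, does not say whether the test is one- or two-sided, and does not say which SD 119.4 s is. The target is then raised to 45 for up to 10% loss.
- **Primary test (Data Analysis).** "Comparisons between BDs and placebo data will be analyzed via 1-sided" t tests or Wilcoxon tests for T_lim.
- **Threshold (Data Analysis).** P "values <.05 indicate statistical significance". It is not halved for the one-sided test.
- **Abstract, Methods.** The same rule is repeated: "Data will be compared using 1-sided" t or Wilcoxon tests, at a 5% level.

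A one-sided 2.5% level appears nowhere, and no reason is given for choosing a one-sided test.

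**The concern.** A sample size and its power belong to one particular test at one particular alpha. Here N, power, effect, SD, sidedness and threshold are all stated, so they can be checked against each other, and they do not fit. The figure of 39 looks like the output of a two-sided calculation, while the claim will be judged by a more lenient one-sided rule.

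Three things are at stake. The first is the evidence needed to claim that bronchodilators lengthen T_lim, which is lower than the sample size suggests. The second is that the primary test as written has no way to declare a shortening. The third is that a reader cannot tell which error rate the trial was designed around, because the 80% is not the power of the planned analysis.

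**Working it through.** **Inputs, all from Data Analysis.** Difference 55.2 s; SD 119.4 s; power 80%; N = 39; test one-sided; threshold P<.05. Assumption: 119.4 s is the SD of the within-patient differences. The standardised effect is then 55.2 / 119.4 = 0.4623.

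**Step 1. Reproduce the stated 39.** Normal approximation: n = [(z for alpha + z for power) / 0.4623]².

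- Two-sided 5%: [(1.960 + 0.842) / 0.4623]² = 36.7, so 37.
- One-sided 5%: [(1.645 + 0.842) / 0.4623]² = 28.9, so 29.

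Exact paired t, using the noncentral t distribution with n − 1 degrees of freedom and noncentrality 0.4623 × √n:

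| Test | Power just below target | Smallest n reaching 80% | Power at 39 | Power at 45 |
|---|---|---|---|---|
| Two-sided 5% | 79.3% at n=38 | 39 (80.3%) | 80.3% | 85.8% |
| One-sided 5% (as planned) | 79.6% at n=30 | 31 (80.8%) | 88.3% | 92.1% |

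The two-sided test returns the stated 39 exactly. One-sided 2.5% is equivalent. A crossover t test with n − 2 degrees of freedom gives the same two answers, 39 and 31.

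**Step 2. Try other one-sided 5% routes to 39.**

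- Wilcoxon instead of t: 32 at an assumed relative efficiency of 0.955, and 36 at 0.864.
- Higher power: 36 for 85% and 42 for 90%.
- 119.4 s as a per-condition SD: the SD of the differences becomes 119.4 × √[2(1 − ρ)], so n = 28.93 × 2(1 − ρ). This equals 39 at ρ = 1 − 39 / (2 × 28.93) = 0.33. Assumed correlations from 0.3 to 0.7 give 41 down to 18.

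Only the last route reaches 39, and only at one particular low correlation that the article does not mention.

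**Step 3. Consequence for the decision rule at n = 39.** The standard error is 119.4 / √39 = 19.12 s.

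- One-sided 5%: 1.686 × 19.12 = 32.2 s mean gain needed.
- Two-sided 5%: 2.024 × 19.12 = 38.7 s mean gain needed.

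The chance of falsely claiming benefit is 5% under the first rule and 2.5% under the second.

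**Step 4. Evaluable patients.** The Results section reports 39 consented by May 2025, one excluded and six not completing, so at most 39 − 1 − 6 = 32 completers at that date. At 32, power is 81.9% one-sided and 71.7% two-sided. If the same loss (7 / 39 = 18%) continued, 45 enrolled would give about 45 × 32 / 39 = 37 completers, with 78.1% power two-sided.

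**The case against.** **The two-sided basis is inferred.** The sample-size sentence states neither alpha nor sidedness and does not define the SD, so it would go too far to say that 39 can arise only from a two-sided test. This stands as a limit on the point. It does not remove it: the simplest paired reading gives 39 exactly, and the one-sided alternative needs an unstated correlation near 0.33.

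**The 5% error rate is disclosed.** A reader might infer that the article misstates its false-positive rate. It does not. Both places openly give a one-sided test at 5%, and the test has that rate. The 2.5% is what the calculation reproducing N would give; the article never promises it.

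**The planned test is not short of power.** A reader might infer from the mismatch that the trial is too small. For the planned test the reverse holds: 80% understates its power.

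**There is a directional rationale.** The Introduction and Discussion argue by analogy with COPD that bronchodilators should lengthen exercise. That supports the expected direction, but it does not show that a shorter T_lim is impossible or of no interest. It is also tempting to cite the tiotropium trial, for which the Introduction reports "there was no difference in the quality of life, chronic cough, exercise capacity" as well as other null findings. That carries little weight. A null result is not evidence of harm, and the Discussion discounts it because exercise capacity was not that trial's primary end point and was measured by a walk test. Nor is it the only bronchodilator trial cited: the Introduction also describes one of a long-acting β-2 agonist with an inhaled corticosteroid, without an exercise result.

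**Non-directional tests for the kinematics are no contradiction.** ANOVA and Friedman tests are non-directional by construction and serve secondary outcomes. This objection stands.

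**Conclusion.** The point holds in this form: the stated N and power do not match the stated primary test. If 119.4 s is the SD of the within-patient differences, 39 is the smallest number giving 80% power at two-sided 5% (80.3%). The planned one-sided 5% test needs 31 and has 88.3% power at 39. Compared with the test that reproduces N, the planned rule doubles the chance of falsely claiming benefit from 2.5% to 5%, lowers the mean gain needed at n=39 by 38.7 − 32.2 = 6.5 s, and leaves a shortening of T_lim undeclarable, with no reason given for ruling it out.

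With at most 32 completers by May 2025, sidedness decides whether power is above or below 80%. A reader might infer that the one-sided rule was chosen for that reason. Nothing in the article supports this; it is simply a reason to settle the matter openly before analysis.

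**What to change.** In Data Analysis and in the Abstract, test T_lim two-sided at 5%, or equivalently for the benefit claim one-sided at 2.5%, and report the two-sided 95% confidence interval for the mean difference. In the sample-size sentence, state alpha, sidedness, and that 119.4 s is the SD of the within-patient differences, if it is. The figure of 39 then stands.

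If one-sided 5% is kept, give the reason for excluding the other direction and restate the power as about 88% at n=39, with 31 as the number needed for 80%.

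Whichever is chosen, the change should be dated before the analysis begins.

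**Cost.** The edits are a few words, but two-sided testing is not free. The mean gain needed at n=39 rises from 32.2 s to 38.7 s. Two-sided power of 80% holds only with about 39 evaluable patients: it is 71.7% at 32, 78.1% at 37 and 85.8% at 45. No increase over the planned 45 is needed if losses stay near the assumed 10% (39 / 0.9 = 43.3, so 44). If losses continue at the rate seen to May 2025, two-sided power would end slightly under 80%.

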### Experimental Design

Patients will be evaluated on 3 nonconsecutive days. Clinical data (anthropometrical and bronchiectasis severity assessed by FACED [FEV1% predicted score, Age, Chronic colonization by *Pseudomonas aeruginosa*, Radiological extension, Dyspnea]) [10] will be obtained from the participants’ medical records. On day 1, pulmonary function will be assessed via whole-body plethysmography, and the maximal exercise capacity will be measured via a cardiopulmonary exercise test (CPET) to obtain the peak work rate (W_peak_). On day 2, patients will be randomly allocated to receive BDs (160 µg of ipratropium bromide and 400 µg of fenoterol hydrobromide) or a placebo (norflurane or HFA134A, a harmless propellant), followed by simultaneous assessments of endurance exercise capacity (constant work-rate exercise test, CWRET) and thoracoabdominal kinematics (optoelectronic plethysmography). On day 3, after at least 1-week washout with no maximum deadline, the patient will repeat the same assessment as on day 2 in the reverse order. This washout period was defined according to the maximum BD withholding time (48 hours) [22], aiming to minimize the carryover effect. In case of NCFB exacerbation during the washout period, a 30-day recovery interval will be performed for the next assessment. Spirometric evaluations will be performed pre-CWRET before and after BDs or placebo. The time to the limit of tolerance (T_lim_) will be obtained under both conditions (BDs and placebo). Thoracoabdominal kinematics will be assessed at 3 time points: at rest (T1), during the unloaded exercise (T2), and at 75% W_peak_ obtained from CPET (T3). Thoracoabdominal kinematics will assess volume variables, including total chest wall volume, compartmental volume, and TAA. The assessor and patient will be blinded to the intervention (BDs or placebo). All exercise tests will be performed on a cycle ergometer (Figure 2).

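### The count of patients passing the 60-second threshold is compared with an independent-groups test although the same patients supply both counts, and the reference for the 60 seconds is not stated

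*Protocol article*

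**What the plan says.** Study Design states the design: "This is a randomized, placebo-controlled, double-blind, crossover trial". Under Experimental Design, on day 3 "the patient will repeat the same assessment as on day 2 in the reverse order", and endurance time (T_lim) "will be obtained under both conditions (BDs and placebo"). Each patient therefore has one post-dose T_lim on BD and one on placebo.

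The responder analysis is one sentence in Data Analysis. It takes the number of participants who "achieved the minimum clinically important difference (>60 seconds) in CWRET between BDs and placebo will be compared via chi-square tests". The Methods paragraph of the abstract gives the general rule: "Categorical data will be analyzed using the chi-square test or Fisher test". The article names no paired test for categorical data.

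For a possible reference value, the schedule gives this:

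- Day 1 has lung function and an incremental test: "the maximal exercise capacity will be measured via a cardiopulmonary exercise test (CPET) to obtain the peak work rate" (W_peak). No constant work-rate test (CWRET) is listed.
- On days 2 and 3 the measurement made both before and after dosing is spirometry: "Spirometric evaluations will be performed pre-CWRET before and after BDs or placebo".
- CWRET Analysis mentions a baseline T_lim, but only as the trigger for adjusting the work rate and repeating the test. It has no place in the three-visit schedule and is not linked to the responder count.

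**The concern.** There are two linked problems.

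First, a difference of more than 60 s needs a reference. If the reference is the other condition, each patient gives a single yes or no (BD minus placebo above 60 s or not). That is one count, with no second count to compare it with. If the reference is a baseline CWRET, there are two counts, but the article does not say that this test is the reference or when it is done.

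Second, under any reading that gives two counts, both come from the same patients. A Pearson chi-square or Fisher test on a table of 2 × 39 supposedly independent observations uses the wrong variance for the difference between the proportions.

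At stake is the p-value attached to the 60 s threshold. The effect assumed for the sample size, 55.2 s, lies just under that threshold, so readers may well look to the responder count for clinical relevance.

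**Working it through.** **Inputs.** From Data Analysis: difference 55.2 s, SD 119.4 s, N = 39 evaluable, 80% power, significance level 5%. From Primary Outcome: threshold 60 s. Assumptions: differences in T_lim are normal, and 119.4 s is the SD of within-patient differences. The tests below are two-sided at 5%.

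**Step 1: the plan's own N.** For a paired t test with noncentrality (55.2/119.4) × √n, two-sided 5%:

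- n = 38 gives power 0.793, and n = 39 gives 0.803. The stated 39 is reproduced.
- Independent groups would need 74 per arm two-sided or 58 per arm one-sided (normal approximation).

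So 119.4 s works as the SD of paired differences, and the sample size relies on the pairing that the responder test drops.

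**Step 2: how many patients pass 60 s.** Let D = BD minus placebo.

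- No effect: P(D > 60) = 1 − Φ(60/119.4) = 1 − Φ(0.503) = 0.308, about 12 of 39. By symmetry P(D < −60) is also 0.308.
- True gain of 55.2 s: P(D > 60) = 1 − Φ(4.8/119.4) = 1 − Φ(0.040) = 0.484, about 19 of 39. P(D < −60) = Φ(−115.2/119.4) = Φ(−0.965) = 0.167.

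A lone BD count near 31% is thus expected with no drug effect at all.

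**Step 3: reading A, better by more than 60 s on BD against better by more than 60 s on placebo.** No patient can be in both groups, so the counts are negatively correlated. With p = 0.308 under no effect, the variance of the difference in proportions is:

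- actual: 2p/n = 0.615/n
- assumed by the independent-groups test: 2p(1 − p)/n = 0.426/n

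The ratio is 1/(1 − p) = 1.44. The large-sample error rate is 2 × [1 − Φ(1.96 × √0.692)] = 0.103. Summing the exact multinomial probabilities at n = 39 gives:

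| Test | Error rate with no effect |
|---|---|
| Pearson chi-square, uncorrected | 10.8% |
| Chi-square with Yates correction | 6.5% |
| Fisher | 6.5% |
| McNemar, uncorrected | 5.4% |
| Exact McNemar | 2.9% |

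At n = 45 the uncorrected chi-square is again at 10.8% and exact McNemar at 3.0%.

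**Step 4: reading B, each condition against a shared baseline T_lim.** Both changes subtract the same baseline, so the counts are positively correlated. Assume equal, independent test-to-test error with SD 119.4/√2 = 84.4 s. The correlation between the two yes/no indicators is then about 0.32. The simulated error rate at n = 39 is 1.9% for the uncorrected chi-square, 4.3% for McNemar and 2.3% for exact McNemar. With a true shift of 55.2 s (responders 48% against 31%), power is 0.33, 0.46 and 0.37 respectively.

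The correlation is not in the article. Over a range of 0.2 to 0.7, the large-sample error rate 2 × [1 − Φ(1.96/√(1 − φ))] falls from 2.8% to 0.03%.

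**The case against.** **McNemar's test is itself a chi-square statistic.** The sentence could mean that test. But the abstract pairs chi-square with Fisher, which points to the independent-groups test, and nothing in the article names a paired one. This leaves some ambiguity and does not rescue the sentence.

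**A baseline T_lim is mentioned.** It could be the intended reference, and a fuller protocol may say so. This stands in part: the right description is that the reference is not stated, and a missing detail of that kind would not by itself be a fault in a condensed article. But the article does name the test, and that test does not suit paired counts whichever reference was meant.

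**A reader might infer that the analysis cannot be run.** That goes too far. A single proportion can be tested with a one-sample chi-square, although it needs a comparison proportion that the article does not give. Two counts can also be formed under either reading above.

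**A reader might infer that the test inflates false positives.** This holds only under reading A. Under reading B the same test is conservative and loses power.

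**A reader might take this as the trial's only test of clinical relevance and a threat to its main result.** The article does not support that. The count is listed neither as a primary nor as a secondary outcome, and the estimated T_lim difference can be read directly against 60 s.

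**Conclusion.** Wrong as written, and it should be fixed. The named test assumes independent groups, whereas the crossover gives two results per patient. The actual error rate at n = 39 is about 11% (about 6.5% with Yates or Fisher) under reading A, and about 2% with reduced power under reading B. Because the reference is not stated, the article does not settle which applies.

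The sizes rest on normal differences and on 119.4 s being the within-patient SD, which the reproduction of N = 39 supports. Reading B also rests on an assumed correlation. The mismatch between test and design depends on none of these.

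The consequence is limited to a supportive analysis. The primary T_lim comparison, the sample size and the models for carryover, period and sequence are unaffected.

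**What to change.** State the reference for the 60 s difference, and replace the chi-square or Fisher test for this comparison with a paired one.

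- **If the reference is the other condition:** report the proportion more than 60 s better on BD and the proportion more than 60 s better on placebo. Compare the two with the exact McNemar (sign) test and give a paired confidence interval for the difference. Showing both proportions matters, because about 31% would pass on BD with no effect.
- **If a baseline CWRET is the reference:** say so, say when it is performed, and still use McNemar or another paired method.

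This costs one or two sentences in Data Analysis and a matching edit to the abstract. It needs no new measurement for the first option and no change to the sample size. When the article was written, data collection was still expected to run to November 2025, so the choice could be fixed before results were seen.
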